### 3.1.2 Treatment Phase

The treatment phase consists of induction therapy, maintenance therapy and re-induction. Subjects who cannot be randomized after induction therapy will have an End of Treatment visit and will be followed-up for survival only. Randomized patients will enter the maintenance phase until they experience disease progression demonstrated by computed tomography (CT) or magnetic resonance imaging (MRI) according to RECIST Version 1.1. Upon progression, patients will undergo re-induction with mFOLFOX6. Re-induction treatment will be continued until progression of disease is demonstrated by CT or MRI. Study treatment will end in case of disease progression during re-induction, or unacceptable toxicities occurring in individual subjects, or consent is withdrawn.

### 3.1.3 End of Treatment Visit

Patients that discontinue from treatment, regardless of the reason, will perform an End of Treatment assessment 4 weeks (+ 7 days) after Day 1 of the last chemotherapy cycle.

### 3.1.4 Follow-Up Phase

All patients should be followed. Follow-up evaluations will be performed every 3 months in order to collect information on survival status. Those patients who discontinue study treatment prematurely, i.e., prior to documented disease progression during maintenance or re-induction phase, will remain in the study and will undergo tumor assessments every 8 weeks until progression of disease is demonstrated by CT- or MRI-scan. Thereafter, patients will be followed for survival status every 3 months.

Details of the study schedule are illustrated in the study flow chart (page 11).

### 3.2 Assignment of Patients to Treatment

According to section 8, a total of approx. 400 patients will be enrolled to reach the planned number of 272 randomizations.

Patients who experience CR/PR or SD 12 weeks after induction therapy and qualify for subsequent maintenance treatment and re-induction treatment with all drug components will be allocated by means of a computer-generated randomization list in a 1:1 ratio to maintenance chemotherapy plus/ minus panitumumab.

The randomization list will be prepared by a statistician using validated SAS software.

Randomization will be performed using a stratified permuted block technique. The block length will be unknown to the centers. To increase homogeneity between the two treatment arms, randomization will be stratified by

- Response to induction therapy at time of randomization (CR/PR vs. SD)
- Prior oxaliplatin-containing adjuvant therapy (yes vs. no)
- Planned starting dose of panitumumab for maintenance therapy, if patient will be assigned to arm A (full dosage vs. reduced dosage)

Registration and randomization are organized centrally by ClinAssess, Germany. If, after check of eligibility a patient who fulfills the inclusion/exclusion parameters is to be included, the center will complete a registration form and fax this page to

ClinAssess GmbH

[contact]

Patients who experience CR/PR or SD 12 weeks after induction therapy and qualify for subsequent maintenance treatment and re-induction treatment with all drug components will be randomized. A randomization form will be sent via fax to ClinAssess, Germany, confirming presence of CR/ PR or SD and qualification for subsequent treatment, as well as providing details for stratification.

Registration forms are accepted at working days between 08:00 am and 06:00 pm. At ClinAssess, forms will be checked, a patient number will be assigned and the confirmation of study participation and treatment assignment of the patient will be faxed back to the center. The first planned dose of induction chemotherapy and panitumumab will be administered no more than 7 days following registration.

Randomizations will be conducted via eCRF.

### 3.3 Centers

An approximate number of 95 centers in Germany will participate in the study. Each center is expected to recruit approximately 4-6 patients starting the induction phase until the planned total number of approx. 400 patients or 272 randomizations respectively is reached.

### 3.4 Study Duration

The study is planned to start in Q4 2013 with respect to first patient in (FPI) including a recruitment period of approx. 84 months, hence the last patient in will be included not prior to Q4 2020. The length of treatment will be approximately 1 year, leading to the last patient off study-treatment approx. in Q4 2021. The total number of events (progressions or deaths, whatever first) required for final analysis of PFS will be reached approx. in Q2 2022. In order to obtain mature data, all randomized patients' minimum observation period of 2 years after randomization of the last subject should be available for each patient randomized to the trial. Therefore, last patient out will be expected approx. in Q4 2022.

|                                                  |                   |
|--------------------------------------------------|-------------------|
| Submission to EC/CA:                      | Q3 2013           |
| First Patient in (FPI):                   | Q4 2013           |
| Recruitment Phase:                        | Approx. 84 months |
| Last patient in (LPI):                    | Approx. Q4 2020   |
| Final Analysis of primary study endpoint: | Approx. Q2 2022   |
| Last Patient out (LPO):                   | Approx. Q4 2022   |

## 4 Selection of the Study Population

### 4.1 Target Population

Patients with mCRC in first-line therapy will be eligible for the study. Eligibility criteria are to be fulfilled at the time of registration for induction treatment. Baseline tumor assessment by CT thorax/ abdomen must have taken place within 3 weeks prior to treatment start (day 1 of cycle 1). Under no circumstances are patients, who were once enrolled in this study, permitted to be re-enrolled into the same study. Both male and female patients are eligible for enrollment.

### 4.2 Inclusion Criteria

- Signed written informed consent
- Male or female  $\geq 18$  years of age
- Histologically proven metastatic colorectal cancer
- Geno- or phenotypically excluded dihydropyrimidine dehydrogenase (DPD) deficiency (by genotyping of the DPD-coding gene or by uracil plasmalevel measurement)
- Molecular testing showing RAS wild-type in colorectal carcinoma cells
- Life expectancy  $> 12$  weeks
- At least one measurable lesion according to RECIST 1.1
- Adequate bone marrow, liver, kidney, organ and metabolic function
  - Bone marrow function
    - leukocyte count  $\geq 3.0 \times 10^9/L$
    - ANC  $\geq 1.5 \times 10^9/L$
    - platelet count  $\geq 100 \times 10^9/L$
    - hemoglobin  $\geq 9$  g/dL or 5.59 mmol/L (may be transfused or treated with erythropoietin to maintain/ exceed this level)
  - Hepatic function
    - Total bilirubin  $\leq 1.5 \times UNL$
    - ALT and AST  $\leq 2.5 \times UNL$  (or  $\leq 5 \times UNL$  in presence of liver metastases)
    - AP  $\leq 5 \times UNL$
  - Renal function
    - Creatinine clearance  $\geq 50$  mL/min according to Cockcroft-Gault formula or serum creatinine  $\leq 1.5 \times UNL$
  - Metabolic function
    - Magnesium  $\geq$  lower limit of normal
    - Calcium  $\geq$  lower limit of normal
- ECOG performance status 0 – 1
- Women of child-bearing potential must have a negative pregnancy test

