| Inclusion criteria     | 
 
• Signed written informed consent
 
• Male or female <math>\geq 18</math> years of age
 
• Histologically proven metastatic colorectal cancer
 
• Geno- or phenotypically excluded dihydropyrimidine dehydrogenase (DPD) deficiency (by genotyping of the DPD-coding gene or by uracil plasmalevel measurement)
 
• Molecular testing showing RAS wild-type in colorectal carcinoma cells
 
• Life expectancy <math>> 12</math> weeks
 
• At least one measurable lesion according to RECIST 1.1
 
• Adequate bone marrow, liver, kidney, organ and metabolic function 
 
○ Bone marrow function 
 
○ leukocyte count <math>\geq 3.0 \times 10^9/L</math>
 
○ ANC <math>\geq 1.5 \times 10^9/L</math>
 
○ platelet count <math>\geq 100 \times 10^9/L</math>
 
○ hemoglobin <math>\geq 9</math> g/dL or 5.59 mmol/L (may be transfused or treated with erythropoietin to maintain/exceed this level)
 
 
 
○ Hepatic function 
 
○ Total bilirubin <math>\leq 1.5 \times UNL</math>
 
○ ALT and AST <math>\leq 2.5 \times UNL</math> (or <math>\leq 5 \times UNL</math> in presence of liver metastases)
 
○ AP <math>\leq 5 \times UNL</math>
 
 
 
○ Renal function 
 
○ Creatinine clearance <math>\geq 50</math> mL/ according to Cockcroft-Gault formula or serum creatinine <math>\leq 1.5 \times UNL</math>
 
 
 
○ Metabolic function 
 
○ Magnesium <math>\geq</math> lower limit of normal
 
○ Calcium <math>\geq</math> lower limit of normal
 
 
 
 
 
• ECOG performance status 0 - 1
 
• Women of child-bearing potential must have a negative pregnancy test
 
 |

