### 4.3 Exclusion Criteria

- Previous treatment for colorectal cancer in the metastatic setting with the exception that patients with urgent need of immediate treatment (high tumor load, symptoms) may have received one cycle of any FOLFOX regimen (no capecitabine!) in case of yet unconfirmed RAS status
- Previous EGFR-targeting therapy < 6 months after end of adjuvant therapy (previous chemoradiation for rectal cancer is accepted for inclusion into the trial and does not account as adjuvant therapy)
- Known brain metastases unless adequately treated (surgery or radiotherapy) with no evidence of progression and neurologically stable off anticonvulsants and steroids
- Chronic inflammatory bowel disease
- Peripheral neuropathy  $\geq$  NCI-CTCAE V 4.03 grade 2
- Other previous malignancies with the exception of a history of previous curatively treated basal cell carcinoma of the skin or pre-invasive carcinoma of the cervix or other curatively treated malignant disease without recurrence after at least 5 years of follow-up
- Significant disease that, in the investigator's opinion, would exclude the patient from the study
- History of cardiac disease; defined as:
  - Congestive heart failure > New York Heart Association (NYHA) class 2
  - Active coronary artery disease (myocardial infarction more than 6 months prior to start of study treatment is allowed)
  - Cardiac arrhythmias requiring anti-arrhythmic therapy (beta-blockers or digoxin are permitted)
  - Uncontrolled hypertension (defined as blood pressure  $\geq$  160 mmHg systolic and/or  $\geq$  90 mmHg diastolic on medication)
- Patients with interstitial lung disease, e.g., pneumonitis or pulmonary fibrosis or evidence of interstitial lung disease on baseline chest CT scan
- Known HIV, hepatitis B or C infection
- Known hypersensitivity reaction to any of the study components
- Radiotherapy, major surgery or any investigational drug 21 days before registration
- Pregnancy or lactation or planning to be pregnant during treatment and within 6 months after the end of treatment
- Subject (male or female) is not willing to use highly effective methods of contraception (per institutional standard) during treatment and for at least an additional 6 months after the end of treatment
- Known alcohol or drug abuse

- Any condition that is unstable or could jeopardize the safety of the patient and his compliance in the study

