## 6.2.2 Preparation and Administration of chemotherapy

All drugs used in the study are labeled for treatment of advanced colorectal cancer. Clinical use and administration should follow the respective product/prescribing information. Administration of mFOLFOX6 or 5-FU/ FA chemotherapy will commence on day 1 of each treatment cycle. Chemotherapy will be administered after administration of panitumumab.

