**Table 2: Chemotherapy dose modification in case of hematological or non-hematological toxicity**

| CTC grade                          | Percent of initial chemotherapy dose |
|------------------------------------|--------------------------------------|
| 0 - 2                              | 100%                                 |
| 3 - 4                              | 75%                                  |
| 3 - 4 (2 nd occurrence) | 50%                                  |

If a grade 3 or 4 toxicity occurs after two dose reductions, the patient is taken off treatment. If the pre-conditions for the start of a new course (according to section 6.4) are not met, treatment should be delayed up to a maximum of 3 weeks.

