### 6.3.2.4 Discontinuation of therapy

In the event that chemotherapy administration is discontinued for any reason prior to disease progression, panitumumab may continue as mono-therapy. During mono-therapy, panitumumab infusions should remain on a once every 14 days ( $\pm$  2 days) schedule until the subject develops disease progression or is unable to tolerate panitumumab mono-therapy.

In the event that oxaliplatin administration is discontinued for any reason prior to disease progression, 5-FU/ FA (and panitumumab if applicable) may continue on a once every 14 days ( $\pm$  2 days) schedule until the subject develops disease progression or intolerance to the therapy.

In the event that panitumumab administration is discontinued for any reason prior to disease progression, chemotherapy may continue. Chemotherapy should remain on a once every 14 days ( $\pm$  2 days) schedule until the subject develops disease progression or is unable to receive chemotherapy.

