#### 6.4 Preconditions for starting a new treatment cycle

The following requirements have to be met, before a new treatment cycle may be administered:

- No hematological toxicity of grade  $\geq 2$  (i.e., ANC  $> 1,500/\mu\text{L}$ , platelets  $> 75,000/\mu\text{L}$ )
- No stomatitis, nausea, vomiting, diarrhea, hand-foot syndrome or other non-hematological toxicity (except for alopecia) of grade  $\geq 2$
- No ongoing requirement for anti-diarrheic treatment
- Bilirubin  $\leq 1.5 \times \text{UNL}$
- Transaminases  $\leq 2.5 \times \text{UNL}$  in patients without liver metastases or  $\leq 5 \times \text{UNL}$  in the presence of hepatic lesions
- No persisting cardiac toxicity
- No peripheral neurotoxicity of grade 3
- Creatinine clearance  $\geq 30 \text{ mL/min}$
- No treatment delay of more than 3 weeks after regularly scheduled dosing date (i.e. 5 weeks after last regular treatment)

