**Appendix 5 - Cockcroft-Gault Formula**

$$\text{Calculated CL}_{\text{CR}} (\text{ml/min}) = \frac{[(140 - \text{subject's age in years}) \times \text{subject's actual body weight in kilograms}]^*}{72 \times \text{subject's serum creatinine (in mg/dL)}}$$

\*: x 0.85 for females

$$\text{Calculated CL}_{\text{CR}} (\text{ml/min}) = \frac{[(140 - \text{subject's age in years}) \times \text{subject's actual body weight in kilograms}] \times K^*}{\text{subject's serum creatinine (in } \mu\text{mol/L)}}$$

K\*: 1.23 for males, 1.05 for females

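### The serum creatinine alternative in the renal entry criterion has no clearance floor, so an eligible patient can have a clearance below the 30 mL/min that section 6.4 requires for a new cycle

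*Protocol*

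**What the plan says.** **Entry.** Section 4.2 treats kidney function as adequate when clearance is at least 50 "mL/min according to Cockcroft-Gault formula or serum creatinine" is no more than 1.5 x UNL. The synopsis has the same two alternatives ("mL/ according to Cockcroft-Gault formula or serum creatinine"). Section 4.3 gives no renal figure, and neither section sets an upper age or a lower weight. The UNL comes from the local laboratory (section 5.1.4).

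**Later cycles.** Section 6.4 opens with "The following requirements have to be met, before a new treatment cycle may be administered" and lists a creatinine clearance of at least 30 mL/min, with no creatinine alternative. For the case where these preconditions fail, the text under Table 2 in section 6.3.2.1 reads "according to section 6.4) are not met, treatment should be delayed up to a maximum of 3 weeks". If chemotherapy is stopped before progression, section 6.3.2.4 says that "panitumumab may continue as mono-therapy".

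**Formula.** Appendix 5 gives the Cockcroft-Gault equation with actual body weight and the factor "x 0.85 for females". Section 5.2.1 has clearance calculated by this formula at screening, in the week before treatment starts.

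**The concern.** A patient who qualifies through creatinine alone is eligible at any clearance, because the two alternatives are joined by "or" and only the first uses clearance. The same serum creatinine means a much lower clearance in an old, light patient than in a young, heavy one. The entry rule can therefore be looser than the rule for starting a further cycle.

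This looks unintended. For the other organ-function items that the two sections share, entry is at least as strict as section 6.4, apart from one boundary value:

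| Item | Entry (4.2) | New cycle (6.4) |
|---|---|---|
| Platelets (x 10^9/L) | at least 100 | above 75 |
| Neutrophils (x 10^9/L) | at least 1.5 | above 1.5 |
| Bilirubin | up to 1.5 x UNL | up to 1.5 x UNL |
| Transaminases (with liver metastases) | up to 2.5 (5) x UNL | up to 2.5 (5) x UNL |
| Clearance (mL/min) | at least 50 | at least 30 |
| Creatinine alternative | up to 1.5 x UNL, any clearance | none |

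Only the last row reverses the order. At stake is the safety of an individual patient at the first dose of mFOLFOX6 plus panitumumab, or a registration that cannot lead to treatment.

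**Working it through.** **Inputs.** From the protocol: the limits 50 mL/min, 1.5 x UNL and 30 mL/min, and the Appendix 5 formula. Assumed, because the protocol gives no UNL: 0.8 to 1.1 mg/dL for women and 1.0 to 1.3 mg/dL for men. The ages and weights are examples.

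**Formula.** CL = (140 - age) x kg x k / (72 x creatinine in mg/dL), with k = 0.85 for women and 1 for men.

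**Step 1: the part that does not depend on creatinine.**
- Woman, 80 years, 50 kg: 60 x 50 x 0.85 / 72 = 35.42
- Woman, 75 years, 55 kg: 65 x 55 x 0.85 / 72 = 42.20
- Man, 82 years, 65 kg: 58 x 65 / 72 = 52.36

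**Step 2: clearance at the highest creatinine that the alternative admits (1.5 x UNL).** The divisors are 1.20, 1.35, 1.50 and 1.65 mg/dL for women, and 1.50, 1.65, 1.80 and 1.95 mg/dL for men.

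| Patient | UNL range (mg/dL) | Clearance (mL/min), lowest to highest UNL |
|---|---|---|
| Woman 80 y, 50 kg | 0.8 / 0.9 / 1.0 / 1.1 | 29.5 / 26.2 / 23.6 / 21.5 |
| Woman 75 y, 55 kg | 0.8 / 0.9 / 1.0 / 1.1 | 35.2 / 31.3 / 28.1 / 25.6 |
| Man 82 y, 65 kg | 1.0 / 1.1 / 1.2 / 1.3 | 34.9 / 31.7 / 29.1 / 26.9 |

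The micromol/L form of the formula in Appendix 5 gives values within 0.3 mL/min of these.

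**Step 3: where the mismatch begins.** Clearance equals 30 at a creatinine of 35.42/30 = 1.181, 42.20/30 = 1.407 and 52.36/30 = 1.745 mg/dL. Dividing by 1.5 gives the UNL above which a mismatch exists at all: 0.79, 0.94 and 1.16 mg/dL. With a UNL of 1.0 for the women and 1.2 for the man, the eligible-but-below-30 bands are 1.18 to 1.50, 1.41 to 1.50 and 1.75 to 1.80 mg/dL.

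**Step 4: how light a patient must be.** For women at 1.5 mg/dL, clearance is below 30 when weight is under 30 x 72 x 1.5 / ((140 - age) x 0.85). That is 54.5 kg at age 70, 58.6 kg at 75 and 63.5 kg at 80.

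**Step 5: how many patients.** The protocol gives no distribution of age, weight or creatinine, so no count follows from it. As an illustration only, a simulation assumed:
- 38% women; mean age 65 (SD 10)
- mean weight 68 kg (SD 14) in women and 82 kg (SD 15) in men
- UNL 1.0 (women) and 1.2 mg/dL (men)
- three log-normal creatinine scenarios: median about 0.70 (women) and 0.89 mg/dL (men) with log-SD 0.25 or 0.30, and about 0.78 and 1.00 with log-SD 0.30

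It put 0.13% to 0.41% of eligible patients below 30 mL/min, or about 0.5 to 1.7 of 400.

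**The case against.** **Section 6.4 may govern cycle 1.** It speaks of a new treatment cycle and does not exempt the first. Section 3.1.1 defines a cycle simply as chemotherapy with or without panitumumab on day 1, and clearance is known before that day. On this reading nobody is dosed below 30. The objection stands in part. The delay item in section 6.4 presupposes an earlier dose, and section 6.3.2.1 invokes 6.4 when discussing the subsequent cycle, so a re-treatment rule is the likelier reading; but the protocol does not say so. A reader might infer that the protocol definitely permits a first dose below 30 mL/min. The text supports that only conditionally.

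**Other safeguards exist.** Section 4.3 excludes "Any condition that is unstable or could jeopardize the safety of the patient and his compliance in the study", and section 6.2.2 says of the chemotherapy that "Clinical use and administration should follow the respective product/prescribing information". These may catch such a patient. Neither puts a renal figure in the protocol, and section 4.2 classes the same patient's kidney function as adequate. What the prescribing information says about renal function cannot be judged from this document.

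**The consequence for cycle 2 is soft.** A reader might infer that the patient is automatically off chemotherapy after one cycle. The three-week limit in section 6.3.2.1 is worded as a recommendation. For longer delays, sections 6.3 and 5.4 ask the investigator to weigh continuation, and clearance may improve. None of this waives the 30 mL/min requirement, but stopping is not automatic, and panitumumab alone may go on.

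**The cases are at the margin.** This stands. All need creatinine close to the ceiling, in patients who must also be ECOG 0 or 1. Two of the three examples show no mismatch at the lower end of the assumed UNL range.

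**Conclusion.** The concern holds as a minor mismatch between the entry criterion and section 6.4. The missing floor is plain in the text. The protocol's own formula gives clearances below 30 mL/min for patients whom section 4.2 admits, subject to the assumed UNL. The consequence depends on how 6.4 is read:

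- If it covers only cycles after the first (likelier), such a patient can receive cycle 1 below the limit and does not meet 6.4 for cycle 2 unless clearance improves.
- If it covers every cycle, the patient is registered but cannot be dosed.

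Neither outcome is useful, and no other section sets a figure that resolves it. The number affected is probably very small, but that is a judgement resting on assumed distributions.

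A reader might also suspect harm to the primary comparison. The document does not support that. Eligibility is settled before induction, which is the same for everyone, and the Full Analysis Population (section 8.3.1) contains only randomized patients who received maintenance treatment. The test of progression-free survival is unaffected.

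**What to change.** In section 4.2 and the synopsis, accept serum creatinine up to 1.5 x UNL only if the calculated Cockcroft-Gault clearance is at least 30 mL/min. The lowest clearance at entry then equals the section 6.4 limit under either reading. A higher floor would be a clinical decision for the sponsor. Leave section 6.4 unchanged: items such as the delay rule do not fit a first cycle.

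Replacing "or" by "and" would be a heavier change. It would raise the minimum to 50 mL/min and, on the same illustrative distributions, exclude at least about 20 to 39 patients per 400.

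**Cost.** Amendment wording in two places. No new test is needed, because clearance is already calculated at screening. The downside is that the rare patient who is eligible only through creatinine, with a clearance below 30, is excluded. The change reaches only patients still to be registered, who may be few. This version is dated 02-Feb-2021. Section 3.4 puts last patient in at about Q4 2020, and the synopsis start of Q2 2014 plus 84 months gives about Q2 2021.
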